## VERSION HISTORY

| Version | Version Date | Description       |
|---------|--------------|-------------------|
| 1.0     | 06FEB2026    | First SAP version |

## LIST OF ABBREVIATIONS

| Abbreviation | Definition                                  |
|--------------|---------------------------------------------|
| ANCOVA       | Analysis of covariance                      |
| BID          | Twice daily                                 |
| CAM          | Confusion Assessment Method                 |
| CI           | Confidence interval                         |
| CRF          | Case report form                            |
| CSR          | Clinical study report                       |
| HR           | Hazard ratio                                |
| ICDSC        | Intensive Care Delirium Screening Checklist |
| ICU          | Intensive care unit                         |
| LOS          | Length of stay                              |
| LS           | Least squares                               |
| mITT         | Modified Intent-to-Treat                    |
| MME          | Milligram morphine equivalent               |
| MMRM         | Mixed model for repeated measures           |
| OR           | Odds ratio                                  |
| SAP          | Statistical analysis plan                   |

## 1 INTRODUCTION

The purpose of this Statistical Analysis Plan (SAP) is to provide a description of the statistical methods to be implemented for the analysis of data from the EPOCH CardioLink-10 Randomized Clinical Trial. The SAP will be finalized prior to database lock.

## 2 STUDY OVERVIEW

### 2.1 Study Objectives

#### 2.1.1 Primary Objective

The primary objective of this study is to evaluate the effect of superficial parasternal intercostal plane (SPIP) blocks with 0.2% ropivacaine on cumulative postoperative opioid use during the 72 hours following catheter insertion into the SPIP.

#### 2.1.2 Secondary Objectives

The secondary objectives of this study include evaluating the effects of superficial parasternal intercostal plane blocks with 0.2% ropivacaine on the following:

- Pain score during the 72 hours following catheter insertion
- Cumulative postoperative opioid use from catheter insertion until discharge from hospital
- Incidence of delirium
- Quality of postoperative recovery

#### 2.1.3 Exploratory Objectives

The exploratory objectives of this study include evaluating the effects of superficial parasternal intercostal plane blocks with 0.2% ropivacaine on the following:

- Time from catheter insertion to extubation
- Time from catheter insertion to first opioid analgesic provision following extubation
- Time from catheter insertion to mobilization
- Intensive care unit (ICU) and hospital length of stay (LOS)
- Incidence of postoperative nausea and vomiting
- Opioid requirements post-discharge
- Chronic post sternotomy pain/disability and patient reported outcomes

### 2.2 Study Design

#### 2.2.1 Overview

EPOCH CardioLink-10 is a randomized, double-blinded, parallel-group, multicentre study of superficial parasternal intercostal plane blocks with 0.2% ropivacaine versus placebo with 0.9% normal saline administered via catheters in the SPIP placed under ultrasound guidance in patients undergoing cardiac surgery through a median sternotomy. Patients meeting inclusion

criteria who provide informed consent will be randomized in a 1:1 fashion into the intervention or control group. Based on the sample size calculation described in Section 2.2.2, approximately 340 participants will need to be randomized to detect important differences. This will be a multicentre trial at 4 sites in Canada, with usual institutional anesthetic and postoperative analgesia management being provided to all enrolled participants. Participants will be followed prospectively during hospitalization with regular assessments of postoperative pain and recovery, as well as during follow-up contacts at 6 weeks and 3-6 months following their operation.

### *2.2.2 Sample Size Determination*

To detect a mean difference of 10 milligram morphine equivalents (MMEs), assuming a standard deviation of 25 and a 2-sided type 1 error rate of 5%, a sample size of 133 participants per group would be required to provide a power of 90%. Assuming an attrition rate of 25%, approximately 340 patients will need to be randomized.

## **2.3 Study Endpoints**

### *2.3.1 Primary Efficacy Endpoints*

The primary efficacy endpoint is to compare the 0.2% ropivacaine group with the placebo group in terms of cumulative postoperative opioid use measured as MMEs during the 72 hours following catheter insertion.

### *2.3.2 Secondary Efficacy Endpoints*

The secondary efficacy endpoints are to compare the 0.2% ropivacaine group with the placebo group in terms of the following:

- Pain score as measured by a standardized numeric rating scale during the 72 hours following catheter insertion
- Cumulative postoperative opioid use measured as MMEs from catheter insertion until discharge from hospital
- Incidence of delirium during the 72 hours following catheter insertion, as defined by the presence of one of the following criteria: Confusion Assessment Method (CAM) or CAM-ICU positive, or Intensive Care Delirium Screening Checklist (ICDSC) >3, or 3D-CAM, or 4AT  $\geq$ 4, or more than one dose of haloperidol or similar antipsychotic drug, or documented delirium by neurologist or psychiatrist consultation
- Quality of Recovery-15 Scale administered 24-96 hours post-surgery

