### 3.3 Secondary Endpoints

- Median pain score as measured by a standardized numeric rating scale over 72 hours following catheter insertion (measured at rest and with coughing q12hours  $\pm$  2 hours post-catheter insertion)
- Cumulative postoperative opioid use measured as Milligram Morphine Equivalent (MME) from catheter insertion until discharge from hospital

- Assessment for delirium BID for 72 hours following catheter insertion, as defined by the presence of one of the following criteria: Confusion Assessment Method (CAM) or CAM-ICU positive, or Intensive Care Delirium Screening Checklist (ICDSC) >3, or 3D-CAM, or 4AT  $\geq 4$ , or more than one dose of haloperidol or similar antipsychotic drug, or documented delirium by neurologist or psychiatrist consultation
- Quality of Recovery-15 Scale administered 24-96 hours post-surgery

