### 3.4 Tertiary (exploratory) Endpoints

- Time from catheter insertion to extubation
- Time from catheter insertion to first opioid analgesic provision following extubation
- Time from catheter insertion to mobilization
- ICU and hospital LOS
- Postoperative nausea and vomiting, measured via a 10-point visual analogue scale BID and antiemetic medication requirements up to 72 hours following catheter insertion
- Opioid requirements post-discharge as assessed by prescriptions provided at time of discharge and during post-discharge follow-up visit using both patient health record and direct patient recounting
- Chronic post sternotomy pain/disability and patient reported outcomes assessed at 3 months  $\pm$  4 weeks from surgery with McGill Pain Questionnaire as well as at 6 weeks  $\pm$  2 weeks and 3 months  $\pm$  4 weeks with the change in PROMIS 29 score (Attempts to obtain the 3-month data can continue for up to 6 months post-surgery before it will be considered a protocol deviation or the participant deemed lost-to-follow-up)

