### 4.2 Exclusion Criteria

1. Redo sternotomy, or cardiac surgery performed through non-sternotomy approaches (minimally invasive procedures, thoracotomies, mini-sternotomy, hemi-sternotomy, etc.)
2. Emergency procedures (surgery within 2 hours)
3. Clinical instability which in the judgement of the investigator precludes enrollment or participation in the study.
4. Weight < 50 kg
5. Active systemic bacterial infection including infective endocarditis or pre-existing sternal infections
6. Surgery for infective endocarditis
7. Pregnancy or nursing
8. Chronic opioid/narcotic use > 6 weeks, active use of illicit drugs, long-term opioid exposure or opioid use and/or chronic pain disorder/syndromes
9. Allergies to amide anesthetic agents or any components of study interventions
10. Inability to comply with, or participate in, protocol (i.e. cognitive impairment/altered mental status/neurological deficit or disorder, inability to provide informed consent, inability to complete pain rating scales, etc.)
11. Receipt of an investigational drug or device within past 7 days

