### 5.2 Study Visits

#### *Visit S: Screening*

- Written informed consent
- Determination of eligibility
- Demographics, medical history, baseline medications including doses
- Physical examination, height and weight assessment, BMI
- Vital signs
- Laboratory assessments: CBC, creatinine/eGFR, electrolytes, coagulation testing
- Preoperative PROMIS 29 Score

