### *2.3.3 Exploratory Efficacy Endpoints*

The exploratory efficacy endpoints are to compare the 0.2% ropivacaine group with the placebo group in terms of the following:

- Time from catheter insertion to extubation
- Time from catheter insertion to first opioid analgesic provision following extubation
- Time from catheter insertion to mobilization
- ICU and hospital LOS

- Incidence of postoperative nausea or vomiting, measured via a 10-point visual analogue scale twice daily (BID) and antiemetic medication requirements during the 72 hours following catheter insertion
- Opioid requirements post-discharge as assessed by prescriptions provided at time of discharge and during post-discharge follow-up visit using both patient health record and direct patient recounting
- Chronic post sternotomy pain/disability and patient reported outcomes assessed with the McGill Pain Questionnaire and PROMIS 29 score

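### The delirium definition scores continued home antipsychotics as delirium, which dilutes the odds ratio by an unknown amount

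*Combined protocol and SAP*

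**What the plan says.** Protocol 3.3 gives a list of ways to be classed as delirious, "as defined by the presence of one of the following criteria". SAP 2.3.2 repeats the list for "Incidence of delirium during the 72 hours following catheter insertion". Most entries are screening instruments (CAM or CAM-ICU, ICDSC, 3D-CAM, 4AT), and one is a documented specialist diagnosis. The remaining entry is a treatment record: "more than one dose of haloperidol or similar antipsychotic drug". Neither document requires those doses to be newly started, to be given for delirium or agitation, or to accompany a positive screen. Neither says which drugs count as similar.

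Four other places bear on the point:

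- Protocol 4.2, criterion 10, excludes people unable to take part, with examples such as "cognitive impairment/altered mental status/neurological deficit or disorder". No criterion names psychiatric illness or antipsychotic use.
- The screening visit in Protocol 5.2 records "Demographics, medical history, baseline medications including doses", but the delirium definition does not use this information.
- SAP 2.3.3 has a separate exploratory nausea endpoint that includes "antiemetic medication requirements during the 72 hours following catheter insertion".
- SAP 3.4.2 analyses delirium by one logistic regression on treatment, sex and intraoperative MME. The joint-model sensitivity analysis in that section is for opioid use to discharge. Delirium has no sensitivity analysis.

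**The concern.** A dose count is being used as a diagnosis. A patient on a stable nightly antipsychotic who continues it after surgery receives about three doses in 72 hours (one per night for three nights). That is more than one, so the patient is a delirium case under the written rule whatever the twice-daily assessments show. Nothing in the eligibility criteria keeps such patients out, and nothing in the analysis separates them afterwards.

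These cases carry no information about the block. Medication that was in place before randomization should be equally common in both arms. It adds similar numbers of false cases to each side and pulls the odds ratio towards 1. The cost is a weaker and less interpretable result on one of the four secondary endpoints.

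**Working it through.** **What can be reproduced.** The documents state no delirium rate, no rate of antipsychotic use and no power for this endpoint, so there is no plan figure to check. The finding rests on the wording. The arithmetic below only shows how the size would depend on rates that have to be assumed.

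**Reading the definition.** Take a patient on a home antipsychotic, with all screens negative, no specialist diagnosis and three doses in the window. The screening criteria are not met and the consultation criterion is not met. The drug criterion is met, since 3 > 1. One criterion is enough, so the patient is classed as delirious.

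**Inputs, all assumed except the sample size.**

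- p = true delirium rate: 20% control and 12% ropivacaine, with 10% and 5% as a lower alternative.
- f = share of non-delirious patients who meet the drug criterion for another reason, equal in both arms: 0 to 10%.
- 170 per arm, from 340 randomized 1:1 (SAP 2.2.2), for power at two-sided 0.05.

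**Formulas.** Observed rate = p + (1 − p)f. The odds ratio compares ropivacaine with control. For equal f, the observed risk difference is the true difference times (1 − f).

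Worked case, f = 5%: control 0.20 + 0.80 × 0.05 = 0.240; ropivacaine 0.12 + 0.88 × 0.05 = 0.164. Odds ratio = (0.164/0.836) / (0.240/0.760) = 0.621. False cases make up 0.040/0.240 = 17% of control-arm cases.

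| f | Control | Ropivacaine | Odds ratio | Risk difference | Power |
|---|---|---|---|---|---|
| 0 | 20.0% | 12.0% | 0.545 | 8.0 points | 52% |
| 2% | 21.6% | 13.8% | 0.579 | 7.8 points | 47% |
| 5% | 24.0% | 16.4% | 0.621 | 7.6 points | 41.5% |
| 10% | 28.0% | 20.8% | 0.675 | 7.2 points | 34% |

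With true rates of 10% and 5%, the odds ratio moves from 0.474 at f = 0 to 0.554 at 2% and 0.637 at 5%. At f = 5%, 31% of control-arm cases are false (0.045/0.145).

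The risk difference hardly moves. The odds ratio, which SAP 3.4.2 reports, moves more. Power is low even without misclassification, so the drug criterion is not the main limit on this endpoint.

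**The case against.** The strongest defence is that the drug criterion has a purpose. Assessments are about twice daily and start only once the patient is awake after extubation (Protocol 5.2), so an episode treated between them can escape every screen. The formula above gives no credit for recovering such cases. It treats all true cases as already found and the drug criterion as adding only errors, so it overstates the harm. The amendment summary also explains that the criteria were spelled out so that assessors could judge objectively, drawing on earlier delirium studies. A dose count is objective, whereas indication must be read from the chart. This stands, and it is why the composite should be kept rather than rewritten around indication.

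Two further points stand in part. Exclusion criterion 10 may remove some home users, so f could be small, and nothing in the documents supports values near 10%. The case report form is not available and might already capture indication. Neither point changes what the written definition says.

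A reader might infer something stronger: that antipsychotics given for nausea also count as delirium and, because the block may reduce opioid use and hence nausea, would produce an apparent benefit on delirium where none exists. The wording does not rule this out. With 15% true delirium in both arms, f of 5% versus 3% would give an odds ratio of 0.89, and 10% versus 5% would give 0.78. But the documents nowhere say that haloperidol or a similar drug is used as an antiemetic at these sites, list no antiemetics and give no frequencies. The route would also need more than one such dose within the window in a patient without delirium. It remains a possibility, not a finding.

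**Conclusion.** The point holds on the text of both documents: a screen-negative patient who continues a home antipsychotic is scored as a delirium case. The expected consequence is dilution of the odds ratio. On assumed true rates of 20% and 12%, it would move from 0.545 to 0.58, 0.62 or 0.68 for f of 2%, 5% or 10%. These figures assume equal f in both arms and no true cases recovered by the drug criterion. The real size is unknown and could be slight if home use is rare. Bias between arms is not established. The matter is confined to a secondary endpoint, and correcting it is a cheap improvement.

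**What to change.** In Protocol 3.3 and SAP 2.3.2, add one sentence: continuation of an antipsychotic already on the participant's screening medication list does not meet the drug criterion. Leave the rest of the prespecified composite as it is.

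In SAP 3.4.2, add a sensitivity analysis of delirium that uses the same logistic model but drops cases resting on the drug criterion alone, and report the number of such cases by arm. Where the chart records an antiemetic indication, those doses can also be excluded in the sensitivity analysis. No new indication field is needed. SAP section 1 foresees finalization before database lock. If the definition can no longer be changed by then, the sensitivity analysis and the count by arm would still show how far the result depends on this criterion.

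The cost is a check against medication data already collected at screening and a little more analysis. The downside is that a few true cases detected only through drug treatment would be missed, either in the sensitivity analysis or among home users.

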### *2.3.3 Exploratory Efficacy Endpoints*

The exploratory efficacy endpoints are to compare the 0.2% ropivacaine group with the placebo group in terms of the following:

- Time from catheter insertion to extubation
- Time from catheter insertion to first opioid analgesic provision following extubation
- Time from catheter insertion to mobilization
- ICU and hospital LOS

- Incidence of postoperative nausea or vomiting, measured via a 10-point visual analogue scale twice daily (BID) and antiemetic medication requirements during the 72 hours following catheter insertion
- Opioid requirements post-discharge as assessed by prescriptions provided at time of discharge and during post-discharge follow-up visit using both patient health record and direct patient recounting
- Chronic post sternotomy pain/disability and patient reported outcomes assessed with the McGill Pain Questionnaire and PROMIS 29 score

#### 2.3.4 Safety Endpoints

The safety endpoints include the following:

- Postoperative laboratory tests
- Postoperative transfusions

### 3 STATISTICAL METHODOLOGY

#### 3.1 General Considerations

##### 3.1.1 Analysis Day

Analysis day will be calculated from the date of first dose of study treatment. The day of the first dose of study treatment will be Day 0 and the day immediately after Day 0 will be Day 1.

##### 3.1.2 Analysis Visits

Scheduled visits will be assigned to analysis visits as recorded on the case report form (CRF).

For each analysis visit, if a scheduled visit occurs within the analysis day window, then the measurement from this scheduled visit will be used. If no scheduled visit occurs or laboratory results of the scheduled visit were unreportable, the unscheduled measurement closest to the target day will be used. If measurements are equidistant to the target day, the later will be used.

| Analysis Visit             | Target Analysis Day | Low Analysis Day | High Analysis Day |
|-----------------------------------|----------------------------|-------------------------|--------------------------|
| Day 0 (day of catheter insertion) | 0                          | 0                       | 0                        |
| Day 42 (phone call visit)         | 42                         | 28                      | 56                       |
| Day 91 (phone call visit)         | 91                         | 63                      | 119                      |

##### 3.1.3 Definition of Baseline

Baseline is defined as the last measurement prior to the first dose of study treatment, unless otherwise stated.

##### 3.1.4 Summary Statistics

Categorical data will generally be summarized with counts and percentages of subjects. The denominator used for the percentage calculation will be clearly defined. Continuous data will

generally be summarized with descriptive statistics including n (number of non-missing values), mean, median, standard deviation, quartile 1, quartile 3, minimum, and maximum.

### 3.1.5 Hypothesis Testing

The hypothesis testing of cumulative postoperative opioid use measured as MMEs up to 72 hours following catheter insertion is statistically defined as:

$$H_0: m_1 - m_0 = 0, H_1: m_1 - m_0 \neq 0,$$

where  $m_0$  - the mean in the placebo group,

$m_1$  - the mean in the 0.2% ropivacaine group.

No adjustment for multiple comparisons will be made.

### 3.1.6 Handling of Dropouts and Missing Data

The objective is for missing data to be kept to a minimum. Continued efforts will be made to measure endpoints on all participants, including those who prematurely discontinued study treatment.

#### Date Values

In cases of incomplete dates, the missing component(s) will be assumed as the most conservative value possible. For example, if the start date is incomplete, the first day of the month will be imputed for the missing day and January will be imputed for the missing month. If a stop date is incomplete, the last day of the month will be imputed for the missing day and December will be imputed for the missing month. Incomplete start and stop dates will be listed as collected without imputation.

Date imputation will only be used for computational purposes such as treatment-emergent status. Actual date values, as they appear in the original CRFs, will be presented within the data listings.

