In the present investigation, each study visit will include safety monitoring. Adverse effects that will be specifically collected include infection, hematoma/hemorrhage, vascular injury, pneumothorax/hemothorax, allergic reaction/anaphylaxis, postoperative nausea/vomiting, pruritus and LAST. Adverse event data will be reported in the study publication.

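### The SAP's earliest-date rule for incomplete start dates is anti-conservative for adverse events: it can place a post-dose event before the first dose, and would remove it from any treatment-emergent summary

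*Combined protocol and SAP*

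**What the plan says.** SAP 3.1.6, under Date Values, opens with a principle: "In cases of incomplete dates, the missing component(s) will be assumed as the most conservative value possible". It then illustrates the principle for start dates: "if the start date is incomplete, the first day of the month will be imputed for the missing day". A start date that also lacks its month goes back to the beginning of the year. The stated use is: "Date imputation will only be used for computational purposes such as treatment-emergent status". The listings keep the raw entries: "Actual date values, as they appear in the original CRFs, will be presented within the data listings".

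SAP 3.1.1 sets the time origin: "Analysis day will be calculated from the date of first dose of study treatment", and "The day of the first dose of study treatment will be Day 0". That day can be any day of a month.

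SAP 3.5.1 groups adverse events by CRF type and summarises them by treatment group. It does not restrict the summary to treatment-emergent events. The SAP uses the term only under Date Values and never defines it. SAP 3.5 makes all safety reporting descriptive.

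Protocol section 6 says that "each study visit will include safety monitoring". The visits after discharge are telephone calls at 6 weeks and 3 months.

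**The concern.** Which date is conservative depends on the use. For deciding whether a harm began after dosing, the cautious choice counts a doubtful event as treatment-emergent. The SAP's illustration does the opposite: it takes the earliest date the recorded parts allow, even when that date precedes the first dose and the recorded parts are fully compatible with onset after it.

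The error runs one way. Imputing the 1st of the month or January can only move a start date earlier or leave it where it is. A post-dose onset can become a pre-dose one, but never the reverse. Any table, count or flag built on treatment-emergent status could then omit true post-dose events and would gain none in exchange. Because safety is reported descriptively, no later model or test would correct such a count.

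**Working it through.** The plan gives no figure on this point to reproduce. The check applies the rule to every possible dosing date.

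**Inputs**
- Day missing: start = 1st of the recorded month (SAP 3.1.6).
- Day and month missing: start = 1 January of the recorded year (SAP 3.1.6).
- Time origin: date of first dose (SAP 3.1.1).
- Assumption: first doses are spread evenly over the 365 days of a year. Using weekdays only changes the results by about 0.5 percentage points at most.
- Assumption: an event is treatment-emergent if its imputed start is on or after the first-dose date. The SAP gives no definition.
- True onset is *k* days after the first dose.

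**Day missing, month known.** The event is classed as pre-dose when onset falls in the month of dosing and dosing was not on the 1st. In a month of *L* days, the affected dosing days run from 2 to *L* − *k*, so there are *L* − *k* − 1 of them (zero if negative). For *k* up to 27 the sum over twelve months is 365 − 12(*k* + 1). At *k* = 28 only the longer months contribute: 7 × 2 + 4 × 1 = 18.

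**Day and month missing, year known.** The affected dosing days run from day 2 of the year to day 365 − *k*, so there are 364 − *k*.

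| Onset after dose (*k*) | Day missing | Day and month missing |
|---|---|---|
| 0 days | 353/365 = 97% | 364/365 = 99.7% |
| 3 days | 317/365 = 87% | 361/365 = 99% |
| 7 days | 269/365 = 74% | 357/365 = 98% |
| 14 days | 185/365 = 51% | 350/365 = 96% |
| 28 days | 18/365 = 5% | 336/365 = 92% |
| 42 days | 0 | 322/365 = 88% |
| 91 days | 0 | 273/365 = 75% |

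With only the day missing, the share is already zero at *k* = 30, because 31 − 30 − 1 = 0 in the longest months.

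**Worked case.** First dose on 18 March. An onset on 20 March recorded only as March is imputed to 1 March, before the dose. An onset on 2 April recorded only as April is imputed to 1 April, after the dose, and is classified correctly.

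**With a first-dose floor.** If the imputed start is the later of the SAP's date and the first-dose date whenever the known parts match the dosing month and year (or the year), no post-dose onset is classed as pre-dose. This holds for every *k* from 0 to 119 days and both patterns of missing parts.

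**The case against.** The strongest reply is that no planned result is shown to change. A reader might infer that post-block harms will be lost from the safety report and both arms will look safer than they were. The documents do not support that. The one adverse-event summary, in SAP 3.5.1, read as written counts every event whatever its imputed date. The Safety Population (SAP 3.2.2) is defined by catheter placement and dosing, not by event dates. Harms would drop out only if the tables were filtered on treatment-emergent status in practice. This part of the reply stands, and it makes the consequence conditional.

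A reader might also infer that partly dated events in general are moved, above all those reported by telephone after discharge. That goes too far. With the month known, the misplacement is confined to onsets in the month of dosing and is absent at day 42. Late onsets are affected only when both day and month are missing, and nothing in the documents suggests that this is common. The documents do not say how many dates are partial. Early in-hospital events, where the percentages are highest, may usually be fully dated, though that too is an assumption.

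Finally, the rule is offered as an example, covers all start dates including medications, and leaves the raw dates in the listings. All true, but this does not remove the defect. The illustration is the only concrete rule given, treatment-emergent status is the only use named, and for that use the rule runs against the SAP's own principle. Listings let a reader spot a misplaced event, but they do not correct a summary.

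**Conclusion.** The point holds in a limited form. For adverse events, the start-date rule in SAP 3.1.6 is anti-conservative for the use it names, and so contradicts the principle it is meant to illustrate. It misplaces most partly dated events that begin within about two weeks of dosing when the day is missing, and most events throughout follow-up when the month is missing too.

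These percentages are conditional on a date being partial, and they rest on evenly spread dosing dates and on a treatment-emergent definition that I had to supply. The effect on reported safety depends on two things the documents leave open: whether any adverse-event table uses the status, and how many dates are incomplete. It may be small. It is still worth correcting, because the SAP says the status will be derived, the rule derives it wrongly, and the correction costs almost nothing.

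**What to change.** Make three short changes to the SAP before database lock, while the study team is still blinded.

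1. In 3.1.6, add a rule for adverse-event start dates. If the known parts match the month and year of the first dose (or the year, when the month is missing), impute the first-dose date, unless a known stop date is earlier than the first dose. In all other cases, and for medications, keep the current rule.
2. Define a treatment-emergent adverse event by reference to the first-dose date.
3. In 3.5.1, state whether the adverse-event table is restricted to treatment-emergent events or counts all events. If nothing will use the status, say so.

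The cost is a few sentences and minimal programming, with no new data. The downside is that a few events of uncertain timing, some of which may have begun before dosing, will count as treatment-emergent, so the safety counts may look slightly less favourable.
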